**GAIA-Ocean Living Lab**				
	**Art therapy**			
		Physical activity	International Physical Activity Questionnaire for elderly [48] or Global Physical Activity Questionnaire [49]	
		Balance	Berg Balance Scale [44], Activities-Specific Balance Confidence Scale [50], Smart Balance Board (Smartifier Oy)	
		Physiology	Smart devices (Xiaomi Mi Band 5, Samsung Galaxy Watch 3, and CAPTAIN eCoach [51])	
		Stress	Perceived Stress Scale [52]	
**INTRAS**				
	**Gradior Cognitive**			
		Neuropsychological or cognitive assessment	Screening: Montreal Cognitive Assessment [53], Gradior Cognitive	
		Performance characteristics	Gradior Cognitive: % successes, graded cognitive performance scores, mistakes and successes by commission, mistakes by omission, number of performed sessions	
**LiCalab-Mobilab & Care**				
	**Virtual reality mirror therapy**			
		Arm functionality	Fugl-Meyer assessment [54]	
		Pain	Visual analogue scale	
		Range of motion	Wearable wireless T-Sens Motion sensors of the Captiv L7000 (TEA Ergo)	
**UQAM-CRIR**				
	**Teledance**			
		Participation and performance characteristics	Frequency and time of use and active practice time or motor engagement (via OpenTera platform or video recordings)	
		User experience	Short punctual or spot-check surveys (audio and visual or via OpenTera platform)	
**McGILL-UdeM-CRIR**				
	**WALKAGAIN (augmented gait training)**			
		Walking in the community (eg, shopping and visiting a museum)	Qualitative (open-ended question)	
		Single and dual tasking	Assessment of walking (single), walking and reading, and walking in the presence of distractors	
		Movement characteristics (eg, tone, loss of sensation, sensorimotor deficits, and muscle strength)	Inertial measurement units or actigraph units	
		Mobility (eg, balance, gait impairments, and endurance)	Berg Balance Scale [44], 6-minute walk test [41], Mini-Balance Evaluation Systems Test [55], Activities-Specific Balance Confidence Scale [50]	
		Pain	Visual analogue scale	
		Participation	Community Healthy Activities Model Program for Seniors [56]	

##### Short-Arm Human Centrifuge

This small-scale pilot study will be conducted by AUTH in Greece. In this pilot study, the SAHC is used for physical and cognitive rehabilitation to mitigate the detrimental effects of bed rest [20,57] (Figure 2). The objective is to assess the combined effects of artificial gravity and physical activity compared with standard of care in patients with stroke (acute or chronic) and healthy older adults over a period of 3 months (1 hour per session, 3 sessions per week). Participants will be assigned randomly to the SAHC training, standard of care training, or passive control. Data will be collected across the domains of body structure and function, activity, and participation as classified by the World Health Organization International Classification of Functioning, disability, and health, at six time points: at baseline, 4 weeks, 8 weeks, 3 months, and 6- and 12-month follow-ups.

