**Figure 2 figure2:**
[figure not shown]
Short-arm human centrifuge.

Participants will include 30 patients with acute stroke (15 SAHC and 15 passive control) and 30 patients with chronic stroke (15 SAHC and 15 passive control). They will be recruited from the Euromedica-Arogi Rehabilitation Center in Thessaloniki, Greece. The inclusion criteria include the following: individuals aged 18 to 70 years, without psychiatric disorder, without vertigo, without nausea or chronic pain, and without a history of syncope. The exclusion criteria include the following: individuals with a height >2 m, elite athletes, individuals with chronic use of substances (drugs or alcohol), individuals who have had a recent surgery, individuals with current arrhythmias, individuals with severe migraines, pregnant individuals, individuals with epilepsy, individuals with cholelithiasis or kidney stones, individuals with recent wounds from surgery, individuals with recent fractures, individuals with acute inflammation or pain, individuals with newly inserted metal pins or plates, and individuals with newly implanted stents.

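### Centrifuge pilot: the objective and randomisation name a standard-of-care arm, but the stroke places are all allotted to centrifuge training or passive control, and healthy older adults have no stated number or source

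*Protocol article*

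**What the plan says.** All the relevant text is in the Short-Arm Human Centrifuge section of the protocol article.

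- **Objective (first paragraph).** "The objective is to assess the combined effects of artificial gravity and physical activity compared with standard of care in patients with stroke". The population goes beyond stroke: "in patients with stroke (acute or chronic) and healthy older adults over a period of 3 months".
- **Allocation (same paragraph).** "Participants will be assigned randomly to the SAHC training, standard of care training, or passive control". That is three arms, with standard of care training and passive control named separately.
- **Sample (paragraph after Figure 2).** "30 patients with acute stroke (15 SAHC and 15 passive control) and 30 patients with chronic stroke (15 SAHC and 15 passive control". That is two arms, in stroke only.
- **Source (same paragraph).** "They will be recruited from the Euromedica-Arogi Rehabilitation Center in Thessaloniki, Greece". No other source is named.

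Two general statements also bear on this. Site Selection, Sample, and Recruitment lets exact numbers vary between test sites. Data Analysis for phase 2 plans tests of intervention effects over time, effect sizes and a 0.05 significance level.

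**The concern.** The two paragraphs describe different trials. One has three arms, a standard-of-care comparator and a population that includes healthy older adults. The other has two arms, a passive comparator and stroke patients only. This is not detail left to a fuller document: both versions are stated, and they cannot both be carried out.

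The stake is the pilot's own question. If the sample paragraph is followed, no stroke patient is randomised to the comparator in the objective. The comparison that can be made, SAHC against passive control, answers a different question, because the protocol itself treats passive control as distinct from standard of care training. Analysis cannot repair this, since an arm without patients cannot be recovered afterwards. Two site teams reading the section in good faith could also set up different randomisation lists.

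**Working it through.** **Inputs** (all from the Short-Arm Human Centrifuge section)

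- Acute stroke: 30 places, of which 15 SAHC and 15 passive control.
- Chronic stroke: 30 places, of which 15 SAHC and 15 passive control.
- Arms named in the randomisation sentence: 3.
- Comparator in the objective: standard of care.
- Populations in the objective: stroke (acute or chronic) and healthy older adults.

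No effect size, standard deviation or power is given for this pilot, so there is no sample size formula to reproduce. The check is a count.

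**Step 1: reproduce the stated subtotals.** Acute: 15 + 15 = 30. Chronic: 15 + 15 = 30. Both agree with the text. Their sum is 30 + 30 = 60, which the article does not print.

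**Step 2: count the stroke places by arm.**

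| Arm in the randomisation sentence | Acute | Chronic | Total |
|---|---|---|---|
| SAHC training | 15 | 15 | 30 |
| Passive control | 15 | 15 | 30 |
| Standard of care training | 30 − 15 − 15 = 0 | 30 − 15 − 15 = 0 | 0 |

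Each stroke group is used up by two arms, so no stroke place remains for the third.

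**Step 3: look for the healthy older adults.** The objective includes them. The sample paragraph gives them no count, and the only source it names is a rehabilitation centre. Number, source and role are therefore not stated.

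**Step 4: see what a three-arm version would need (illustration only).**

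- Keeping 15 per cell: 3 arms × 2 stroke groups × 15 = 90.
- Keeping the sum of 60 with equal cells: 60 / (3 × 2) = 10 per cell.

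Neither figure is in the article. They show that the three-arm text requires either more places or smaller cells.

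**The case against.** **The two controls may be the same thing.** A rehabilitation centre's passive control could be usual care under another name. This fails on the text, because one sentence offers standard of care training and passive control as alternatives.

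**Numbers are flexible and this is a pilot.** The allowance in Site Selection, Sample, and Recruitment concerns numbers. It does not cover an arm without places or a change of comparator. The project's primary aim is harmonisation of living lab procedures, and the pilots explore effects in small samples. That limits the reach of the problem but does not make this pilot's objective answerable.

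**The list of participants may not be exhaustive.** This stands in part. The wording could leave room for other participants, the eligibility criteria do not themselves require a stroke, and the exclusion of elite athletes would fit a wider cohort. Site Selection, Sample, and Recruitment names only stroke and mild cognitive impairment, but the art therapy pilot recruits healthy people, so that sentence is not decisive. A reader might infer that 0 of 60 places go to healthy adults. But 60 is an unprinted sum of the stroke groups alone, so that zero follows by construction. What the text supports is that their number and source are not given. The argument does not rescue the standard-of-care arm for stroke patients, because both stroke groups are fully split.

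**Three further inferences are tempting but unsupported.**

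- *A contact gap of about 39 hours* (3 one-hour sessions a week × 13 weeks; 36 hours if 3 months is taken as 12 weeks). This assumes that passive control receives no contact, and the article does not define what that arm receives.
- *Passive control means no training.* This is not stated either, and patients recruited at a rehabilitation centre may be receiving therapy.
- *A 22% loss of precision* (√(15/10) = 1.22). This applies only if 60 places are spread over six cells, a split that the article does not state. At 15 per cell there is no such loss.

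**Conclusion.** The contradiction holds as written. Three arms, a standard-of-care comparator and a mixed population are set against two arms, a passive comparator and stroke patients only. Its size is a count: of the 60 stroke places, 30 are SAHC, 30 are passive control and none is standard of care. Healthy older adults have no stated number, source or role.

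That the comparison in the objective cannot be estimated is conditional on the sample paragraph being followed. If the randomisation sentence is the intended one, the fault lies in the places instead. The article does not show which is meant. A reader might also infer that a result against passive control will be reported as a result against standard of care. That would be a prediction about future authors; the text supports only that such a difference would not answer the stated objective.

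This should be settled before the pilot randomises anyone. It concerns one of six pilots and does not touch the harmonisation aim.

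**What to change.** Before randomisation opens, reconcile the objective, the randomisation sentence and the sample paragraph so that arms, comparator, population and places per arm agree.

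- **If two arms are intended:** name the single control arm, define what it receives, and restate the objective and the planned conclusion against it. If the sample paragraph stands, that is SAHC versus passive control. The 60 places are unchanged.
- **If three arms are intended:** state the places per arm in each stroke group and the total. The working shows 90 at 15 per cell, or 10 per cell at 60, as illustrations.
- **In either case:** remove healthy older adults from the objective, or state their number, source and role. Report the comparison within the acute and chronic groups, for which separate counts are given. If randomisation is to be stratified by these groups, say so; the article gives the counts but does not describe stratification.

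**Cost:** protocol wording and possibly an ethics amendment, a route that the Design section already provides for. No extra patients are needed if two arms are kept. A three-arm design needs more patients or smaller cells.

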**Figure 2 figure2:**
[figure not shown]
Short-arm human centrifuge.

Participants will include 30 patients with acute stroke (15 SAHC and 15 passive control) and 30 patients with chronic stroke (15 SAHC and 15 passive control). They will be recruited from the Euromedica-Arogi Rehabilitation Center in Thessaloniki, Greece. The inclusion criteria include the following: individuals aged 18 to 70 years, without psychiatric disorder, without vertigo, without nausea or chronic pain, and without a history of syncope. The exclusion criteria include the following: individuals with a height >2 m, elite athletes, individuals with chronic use of substances (drugs or alcohol), individuals who have had a recent surgery, individuals with current arrhythmias, individuals with severe migraines, pregnant individuals, individuals with epilepsy, individuals with cholelithiasis or kidney stones, individuals with recent wounds from surgery, individuals with recent fractures, individuals with acute inflammation or pain, individuals with newly inserted metal pins or plates, and individuals with newly implanted stents.

The centrifugation on the SAHC will be combined with mild-intensity exercise based on the maximum heart rate. The SAHC intervention consists of 3 sessions per week, each with a duration of 1 hour, for 3 months. The participant is positioned in a supine and horizontal position on the rotation bed, with the head located toward the center. The beds with the patients turn around the axis of rotation with a force that is the product of body mass, distance from the axis of rotation, and angular velocity squared. Initially, there will be 1 session to familiarize participants with the SAHC group and to individually assess the optimal *g* load according to the participant’s cardiovascular functioning with cardiac output, stroke volume, mean arterial pressure, diastolic blood pressure, systolic blood pressure, and heart rate. These criteria are monitored at each training session and are used to dynamically adapt the intervention intensity. More specifically, after 6 training sessions (2 weeks), the centrifugation load will be increased, and centrifugation will be combined with either aerobic exercise (through an ergometer) or resistance training through elastic training bands during centrifugation (depending on cardiovascular criteria). Further verification of the dynamic configuration of the intervention will be provided by the electroencephalographic assessment. Functional connectivity and cortical-network features derived from graph theory will be used by deep learning algorithms (convolutional neural networks) to define the optimal centrifuge training.

##### Art Therapy

This small-scale pilot study will be conducted by GAIA-Ocean Living Lab in Spain. The objective of this small-scale pilot study is to assess the performing art methodologies (music and dance therapy) in different green and public spaces in the area of Gernika-Lumo (Spain) by assessing their feasibility and to explore their potential impact for individuals with stress-related conditions to support the therapists as well as formal and informal caregivers. Data will be collected at two time points: at baseline and after the end of the intervention.

A sample of 20 healthy men and women will be recruited from Gernika-Lumo (Biscay, Spain). Participants will be included if they are aged 18 to 85 years and will be allocated randomly to the testing or control group. Individuals with a medical history of severe cognitive impairment are not eligible to participate.

The performing arts intervention is a form of physical and mental rehabilitation offered to volunteers in public spaces. Each intervention will be conducted by experts on the methodologies for 2 months, twice a week. Participants will be instructed to follow the different activities, and their biometrics will be monitored during the sessions (smartwatch, smart band, and balance board) to assess their performance and compare their progress. At the end of the pilot period, participants in the control group will also have the opportunity to try out the intervention.

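### In the art-therapy pilot the balance board is both a session monitor and one of three balance instruments, so a between-group difference on it may partly reflect familiarity with the device

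*Protocol article*

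**What the plan says.** All statements come from the protocol article, under Small-Scale Pilot Studies (Phase 2).

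- **Outcome listing.** In Table 2 the Balance row for the art-therapy pilot names the Berg Balance Scale and then "Activities-Specific Balance Confidence Scale [50], Smart Balance Board (Smartifier Oy". The board is therefore one of three balance instruments. No order of priority is given.
- **Session use.** The Art Therapy section says of participants in the activities that "their biometrics will be monitored during the sessions (smartwatch, smart band, and balance board) to assess their performance and compare their progress".
- **Design.** "A sample of 20 healthy men and women will be recruited from Gernika-Lumo (Biscay, Spain", and they "will be allocated randomly to the testing or control group". The allocation ratio is not stated.
- **Timing.** "Data will be collected at two time points: at baseline and after the end of the intervention".
- **Session schedule.** "Each intervention will be conducted by experts on the methodologies for 2 months, twice a week".
- **Controls.** At the close of the pilot period, "participants in the control group will also have the opportunity to try out the intervention". No earlier attendance by controls is described.
- **Analysis.** The Data Analysis section for phase 2 gives a general approach: repeated-measures parametric or nonparametric tests, effect sizes, significance at P<.05, and freedom for each pilot to vary.

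**The concern.** The device that measures balance is also used in the sessions of one arm. Between the two assessments the testing group can meet it repeatedly, while no contact is described for controls. If people score better on a board once they are used to it, the final comparison sets practised users against unpractised ones.

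This differs from the question whether controls have board values at all. With complete data in both groups the problem remains, because the unequal exposure belongs to the allocated treatment. Randomisation balances the groups at baseline but not what happens to them afterwards. Baseline adjustment removes differences in starting score but not a gain from device contact in one arm. On this instrument familiarity and true change cannot be told apart in the analysis, so the matter has to be settled in the design.

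At stake is how a board result is read: a difference could be reported as an effect on balance when part or all of it is familiarity.

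**Working it through.** The plan gives no power, effect size or SD for this pilot, so there is no stated figure to reproduce. The check has two parts.

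**1. Exposure to the board between assessments**

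Inputs (Art Therapy section): two sessions a week for 2 months; controls offered the intervention only afterwards.

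- Taking 2 months as 8 weeks: 2 × 8 = 16 sessions.
- Taking 2 months as 61 days: 2 × 61/7 = 17.4, so about 17 sessions.
- Controls: none described.

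The figure of 16 to 17 is a ceiling. It assumes that every participant in the testing group uses the board at every session, which the article does not say.

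**2. What a familiarity shift would do to a group comparison (illustration only)**

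From the document: 20 participants and a 5% significance level. Assumed: 1:1 allocation (10 per group), a two-sided test, an unpaired t test on final values, no true effect on balance, and a familiarity shift of d SD in the testing group.

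- Degrees of freedom: 10 + 10 − 2 = 18; critical value t = 2.101.
- Noncentrality: d × √(10/2) = d × 2.236.
- Rejection probability: P(T > 2.101) + P(T < −2.101), with T noncentral t on 18 df.

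| Shift d (SD) | Noncentrality | Significant in favour of testing | Significant in either direction |
|---|---|---|---|
| 0 | 0 | 2.5% | 5.0% |
| 0.2 | 0.447 | 6.2% | 7.1% |
| 0.5 | 1.118 | 18.4% | 18.5% |
| 0.8 | 1.789 | 39.5% | 39.5% |

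The right reference depends on the column: 5% for rejection in either direction, 2.5% for an apparent benefit.

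Baseline adjustment does not help. With an assumed baseline-to-final correlation of 0.7, the residual SD falls by the factor √(1 − 0.49) = 0.714 and the df become 17. The same shifts are then significant in either direction with probability 9.1%, 31.5% and 65.6%. Adjustment sharpens the comparison but leaves the shift in place, so the shift is detected more often.

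**The case against.** The strongest reply is that the board may not be a between-group outcome at all. Table 2 is an overview of data collection and mixes assessments with process data: the Gradior rows include the number of sessions performed, and the teledance rows include frequency and time of use. The only use of the board that the Art Therapy text describes is session monitoring, and no sentence says that board scores are compared between testing and control. If the board is session data only, the second remedy below may already be the plan. This part stands as an uncertainty. Listing the board under Balance beside two assessment scales, in a randomised design with baseline and final data, makes the outcome reading the natural one, but not the certain one.

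The second reply is that nothing in the documents shows a practice effect. They do not say what the board measures, whether it gives feedback, or how long or how often anyone stands on it. That stands too. A reader might infer that familiarity necessarily raises the score and that the bias always favours the intervention. The documents support neither; they show unequal opportunity for practice, which makes such a bias possible.

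A reader might also infer that the pilot's whole balance result rests on the board. It does not. The Berg Balance Scale and the Activities-Specific Balance Confidence Scale do not use it and allow a cross-check.

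The third reply is that little depends on the point. The pilot's aims are feasibility and exploring potential impact for people with stress-related conditions, balance is one of four outcome domains in its part of Table 2, and no primary outcome is named for it. This limits the consequence but does not remove the point, because the control group serves a comparison and the general analysis section tests intervention effects at P<.05.

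Lastly, a condensed article may leave testing procedure to the full protocol. The absence of familiarisation trials is therefore not held against it. The point rests on the two uses that the article does state.

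**Conclusion.** The point holds in conditional form. Table 2 and the Art Therapy section give the balance board two roles, and only the testing group is described as attending sessions before the final assessment. If board scores are compared between groups, the arms may differ in device contact by up to about 16 to 17 sessions, and a better score may partly reflect familiarity. No later analysis of the board scores can separate the two.

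The size is unknown. Under the assumptions shown (10 per group, two-sided 5%, t test on final values, no true effect), shifts of 0.2 to 0.8 SD raise the chance of a significant difference in either direction from the nominal 5% to between 7.1% and 39.5%. The shifts are illustrative, and the t test on final values is not the article's stated analysis.

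This is a worthwhile, inexpensive improvement to an exploratory pilot. It affects the reading of one of three balance instruments and does not undermine the pilot.

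**What to change.** State the role of the balance board before data collection and choose one of two courses.

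1. **Assessment only.** Use the board at the baseline and final assessments, with the same familiarisation in both groups before the recorded measurement, and monitor sessions with the smartwatch and smart band. Cost: protocol wording and a few minutes per assessment; the in-session balance traces are lost.
2. **Session monitor only.** Keep the board in the sessions, report its values as descriptive process data for the testing group, and base the testing-versus-control balance comparison on the Berg Balance Scale and the Activities-Specific Balance Confidence Scale. Cost: protocol wording; the board is lost as a between-group outcome.

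The second course removes the risk under either reading of Table 2 and adds no measurement, since both scales are already planned.
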